##### Power for Primary Outcome (Hypothesis 3a)

In our prior National Cancer Institute trial, we observed an absolute 9% difference in the standard messaging versus no-messaging control group [29]. We expect socioeconomically disadvantaged groups to have lower cessation rates than non–socioeconomically disadvantaged groups. Thus, we calculated power using a range of control cessation rates from 7% to 9%. We started at 7%, because it is the estimated rate at which the general population of all individuals who smoke quit without any intervention [34]. On the basis of the recommender enhancements (and further pilot data), we saw an additional marginal difference of 6% at 30 days (even higher for African American individuals who smoke) and expect this difference to continue and expand over time as the recommender system continues to learn and adapt to the individual; however, to be conservative and recognizing the potential difficulty in impacting behavior in this population, we chose to power for a small difference, namely 7%. Although our hypothesis is directional, we have chosen to adopt the commonly used conservative approach of 2-sided tests for all our power calculations. On the basis of a 2-sided chi-square test of equal proportions, α=.05, for all these base rates, we will have 80% power with 600 participants (N=300 per arm). Considering loss to follow-up, we plan to oversample by 25% and thus have budgeted for a total of 750 participants to complete baseline and be randomized. On the basis of our prior experience recruiting from clinical systems, we expect the dropout rate to be lower than the 25% we have assumed in our calculations.

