## Results

This trial was funded in April 2020 and is currently ongoing. As of May 2024, we had enrolled 757 participants, and 591 (78.1%) of them had completed the 6-month follow-up interviews (Figure 2). We anticipate that data analysis and final manuscript preparation will occur in late 2025. Multimedia Appendix 3 provides the demographic and screening survey responses of 757 participants.

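### Inflating 600 by 25% to 750 covers loss of up to 20%, not the 25% dropout that the power section says it assumed; at 25% loss power falls by about 2.6 to 2.8 points

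*Protocol article*

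**What the plan says.** All the figures stand in one paragraph of the protocol article, Power for Primary Outcome (Hypothesis 3a).

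- Test: "On the basis of a 2-sided chi-square test of equal proportions, α=.05, for all these base rates".
- Control rates: "we calculated power using a range of control cessation rates from 7% to 9" percent.
- Effect: "we chose to power for a small difference, namely 7" percent, read here as percentage points.
- Requirement: "we will have 80% power with 600 participants (N=300 per arm").
- Allowance for loss: "Considering loss to follow-up, we plan to oversample by 25% and thus have budgeted for a total of 750 participants".
- Closing remark: "we expect the dropout rate to be lower than the 25% we have assumed in our calculations".

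Study Design and Setting repeats 750 as the target. The abstract and the Results section give 757 as the number enrolled.

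**The concern.** An oversample of 25% and a dropout of 25% are different quantities. The first multiplies the required number by 1.25; the second requires dividing it by 0.75. The paragraph does the first and then describes the result as if it had done the second.

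Analysable participants are the right basis for power here. Under Hypothesis 3a: Primary Outcome, the main analysis uses observed outcomes weighted by the inverse probability of being observed, and counting missing as smoking is only a sensitivity analysis. Weighting is meant to deal with bias from missing outcomes; it does not put back the information that the missing participants would have supplied.

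At stake is how the trial's sensitivity will be read. A reader of a null result would take the 80% power as protected against the loss of a quarter of participants. At that loss, the sample falls short of the 600 on which the 80% rests.

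**Working it through.** **Inputs.** All come from the power paragraph: two-sided alpha 0.05 (z = 1.96), equal allocation, control rate pC of 7%, 8% or 9%, difference of 7 points (pT = pC + 0.07), 600 analysable, 750 randomised, 25% dropout. The 757 enrolled comes from Results.

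**Step 1: reproduce the plan's 600.** For the chi-square test with n per arm and p̄ = (pC + pT)/2:

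- SE0 = √[2 p̄(1 − p̄)/n]
- SE1 = √[(pC(1 − pC) + pT(1 − pT))/n]
- power = Φ[(0.07 − 1.96 × SE0)/SE1]

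For 7% against 14% with n = 300: p̄ = 0.105, SE0 = 0.02503, SE1 = 0.02487. Power = Φ[(0.07 − 0.04906)/0.02487] = Φ(0.842) = 80.0%. The stated 600 reproduces exactly at the 7% control rate.

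**Step 2: reproduce the 750.** 600 × 1.25 = 750. This matches the plan.

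**Step 3: the loss that 750 covers.**

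- Largest loss that still leaves 600 of 750: 1 − 600/750 = 20%.
- Left of 750 at 25% loss: 750 × 0.75 = 562.5, which is 37.5 short of 600 (about 281 per arm).
- Number needed to keep 600 at 25% loss: 600/0.75 = 800.
- With the 757 enrolled: 1 − 600/757 = 20.7%, and 757 × 0.75 = 567.75, about 568.

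**Step 4: power at 25% loss.** The formula of step 1 with n = 562.5/2 = 281.25. For 7% against 14%: SE0 = 0.02585, SE1 = 0.02568, power = Φ(0.753) = 77.4%.

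| Control vs intervention | 300 per arm | 25% loss from 750 | Cost of the slip | 25% loss from 757 |
|---|---|---|---|---|
| 7% vs 14% | 80.0% | 77.4% | 2.6 points | 77.8% |
| 8% vs 15% | 76.8% | 74.1% | 2.7 points | 74.5% |
| 9% vs 16% | 73.8% | 71.0% | 2.8 points | 71.4% |

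**Step 5: keep two effects apart.** Only the fourth column belongs to this point. At 8% and 9% the 300-per-arm column is already below 80%, so the claim of 80% power at every base rate fails there with no dropout error at all. That is a separate error in the same paragraph.

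**The case against.** The strongest defence is that oversampling by 25% is a correct way to allow for 20% loss, and that the authors expected to lose fewer than 25%. The first half would settle the matter if the paragraph stopped at the 750. It does not: its last sentence names 25% as the dropout rate assumed. The second half softens the consequence without mending the statement. Loss of 21% to 24% is also lower than 25%, yet leaves 592 down to 570 of 750. The 20% threshold on which the design depends is nowhere stated.

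Other parts of the defence stand, and they limit the point.

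- A reader might infer that there is no allowance for attrition. There is one: it reaches 20% and is 5 percentage points smaller than labelled.
- A reader might charge the whole gap between 80% and 71.0% to this slip. Most of that gap, from 80% to 73.8%, exists at 9% with 300 per arm.
- A reader might take the statement in Results, "As of May 2024, we had enrolled 757 participants, and 591 (78.1%) of them had completed the 6-month follow-up interviews", as a shortfall against 600 that has already happened. The dates do not support this. Recruitment ended in March 2024, the count is from May 2024, and the abstract puts the end of 6-month follow-up in November 2024. The last recruits were not yet due, and 9 more interviews would reach 600.
- A reader might expect carbon monoxide testing to lower the analysable number further. Testing is asked only of self-reported quitters, and the article does not say whether an untested quitter counts as missing or as smoking. In the second case the denominator does not fall.

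**Conclusion.** The point holds in limited form. The sample of 750 is consistent with 600 analysable and loss of up to 20% (20.7% for the 757 enrolled); it is not consistent with 600 analysable and the 25% dropout that the paragraph says it assumed. If 25% were lost, about 562 of 750 (568 of 757) would remain, and power for a 7-point difference would be about 2.6 to 2.8 points lower than at 600 (slightly less with 757): 77.4% in place of 80.0% at the 7% control rate.

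This rests on reading the 7% as an absolute difference, on the uncorrected chi-square test, which reproduces the plan's own 600, and on equal loss in the two arms. It does not establish that the trial is short of participants: the final retention is not in the article, and the cost arises only if loss exceeds 20%. Severity is minor to moderate. The test, the analysis and the sample are unaffected; the stated protection against attrition is what is wrong.

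**What to change.** Replace the statement that 25% dropout was assumed with one saying that a 25% oversample, 750 for a required 600, covers loss of up to 20%. Add that 25% loss would leave about 562 participants, with power for a 7-point difference of about 77% at a 7% control rate, 74% at 8% and 71% at 9%. The claim of 80% power at every base rate should be corrected separately, so that the two effects are not merged.

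The cost is two sentences. Recruitment is complete and no participants are added. The article expects data analysis in late 2025, so the wording could be settled before results are reported.

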##### Hypothesis 3b: Mediation Analysis

Measured internal and external processes will mediate the effect of Adapt2Quit on smoking cessation. Adapt2Quit is expected to result in several interconnected processes (Adapt2Quit increases personal relevance, thereby improving system engagement, which results in increasing the external and internal processes, causing the participant to implement cessation-supporting behaviors resulting in smoking cessation; Figure 1). We will explore the pathways using modern mediation and structural equation modeling (SEM) techniques. Mediation occurs when an independent variable (X) leads to a given outcome (Y) through an intervening process (M). In our case, the independent variable is the Adapt2Quit recommender (X), and the outcome will be 6 months of smoking cessation (Y). Perceived competence and adoption of cessation-facilitating behaviors (use of quitlines, use of NRT, and adoption of behavioral strategies) are all potential mediators (M). The mediation analyses will focus on each individual process variable, using the classic mediation principles modified from Barron and Kenny [44]. This approach requires 3 regression models and decomposes the total effect (*c*) of the independent variable (X) into a direct component (*c’*) and an indirect or mediated component (c-c’). Limitations to the modified Barron and Kenny approach include the fact that more complex mediation pathways with multiple steps are not allowed. Thus, we will implement SEM using Mplus as the covariance analysis software. SEM allows for the simultaneous estimation of multiple regression equations representing complex mediation pathways, allowing errors to be correlated across equations. Furthermore, constructs may be represented as latent variables to relax the assumption of no measurement error. An array of diagnostic tests (eg, root mean square error of approximation and comparative fit index) are available to examine model quality.

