#### Internal Processes

Perceived competence, a key SDT construct, will be measured using the previously validated PCS [23]. The 4-item scale assesses the participant’s feelings of being able to stop smoking permanently (“I feel confident in my ability to not smoke,” “I now feel capable of not smoking,” “I am able to not smoke anymore,” and “I am able to meet the challenge of not smoking”). Responses are scored on a 7-point scale from 1 (strongly disagree) to 7 (strongly agree), and individual items are averaged to create a scale mean. In prior work [23], PCS was reliable (α=.95) at the 6-month follow-up [23]. We will assess PCS at baseline and at the 6-month follow-up visit.

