#### Aim 1: Adapt2Quit Engagement

Aim 1 is analyzed within the intervention group (N=375). Engagement will be defined as the number of daily ratings divided by the total number of rating opportunities (percentage of ratings completed).

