##### Power for Hypothesis 2b

Analysis and the power calculation for time to first call completed is similar to the hypothesis 3b analysis. The use of NRT will be assessed via self-report at the 6-month follow-up. To analyze NRT use, a dichotomous variable, we will create a logistic model with the use of NRT (yes or no) as the dependent variable and randomization as the independent variable.

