#### Aim 3: Effectiveness

##### Hypothesis 3a: Primary Outcome

Adapt2Quit participants will have greater smoking cessation rates (6-month point-prevalence biochemically verified) than control participants. For our primary outcome, we will follow recommendations from the Society for Nicotine and Tobacco Research and other experts. While we will attempt to minimize dropout rates loss to follow-up (missing outcomes) in trials such as ours cannot be fully averted [41]. Penalized imputation (missing=still smoking) is not a conservative approach and can be biased (against a group), especially when there is a differential missing between the groups [41]. Thus, the recommended approach is to use inverse probability weighting [42]. In this approach, the first step is to develop a logistic regression model to predict nonmissingness using variables that are found to be different between study participants with and without missing data. The next step is to calculate the inverse probability of nonmissingness and use it as the weight in a logistic regression model to compare the cessation rate between two study groups [43]. Along with inverse probability weighting, we will present penalized imputation and a complete case analysis (limited to those with complete data) as sensitivity analyses. We propose to biochemically verify participants who self-report quitting smoking using a CO meter.

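### For a yes/no outcome, c minus c' mixes mediation with a scale artefact if the models are logistic, and a 6-month PCS score cannot be placed before quitting

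*Protocol article*

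**What the plan says.** The section on Hypothesis 3b states that "the outcome will be 6 months of smoking cessation (Y", and the section on six-month cessation makes this a yes/no 7-day point-prevalence measure. Each process variable is first analysed singly. "This approach requires 3 regression models and decomposes the total effect" into a direct component c' "and an indirect or mediated component (c-c", that is, c minus c'. No link function is given. The only model that the article states for cessation is in Hypothesis 3a, where the inverse probability is calculated in order to "use it as the weight in a logistic regression model to compare the cessation rate between two study groups".

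The listed mediators are perceived competence and cessation-facilitating behaviours ("use of quitlines, use of NRT, and adoption of behavioral strategies"). Their timing differs:

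- PCS, under Internal Processes: "We will assess PCS at baseline and at the 6-month follow-up visit".
- NRT, under Power for Hypothesis 2b: "The use of NRT will be assessed via self-report at the 6-month follow-up".
- Quitline use, under External Processes and Hypothesis 2b: taken from quitline records as time from baseline to the first completed counsellor call.
- Behavioural strategies: no timing given.

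Structural equation modelling (SEM) is then added for multistep pathways and measurement error. The narrative causal chain passes through engagement. Engagement is defined under Aim 1 as the percentage of ratings completed, and "Aim 1 is analyzed within the intervention group (N=375").

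**The concern.** There are two separate problems.

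The first is scale. In a logistic model, adding any predictor of the outcome changes the treatment coefficient, even when treatment has no effect on that predictor. The difference between the coefficients without and with the mediator is then partly an artefact of the odds-ratio scale.

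The second is order. A mediator must act before the outcome. PCS items ask how able the person feels not to smoke. Asked at the same assessment as abstinence, they may describe the result of quitting.

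Hypothesis 3b is a named hypothesis, and the conclusions commit later papers to the analysis plans in this article. At stake are the mechanism claims: real mediation could be under-reported, or a consequence of quitting could be reported as its cause.

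**Working it through.** The plan gives no mediation figure to reproduce, so the check uses its planning rates.

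**Inputs from the article** (Power for Primary Outcome): control cessation 7% to 9%, difference 7 points. At 7% versus 14%, c = ln(0.14/0.86) - ln(0.07/0.93) = -1.815 + 2.587 = 0.771. At 9% versus 16%, c = 0.655.

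**Assumptions**, because the article gives no values: a is the arm effect on the mediator in SD units; b is the mediator log-odds per SD.

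**Step 1, scale.** Let M = aX + e with e standard normal, and logit P(Y=1) = b0 + c'X + bM. The values of b0 and c' were solved by numerical integration over e so that the marginal rates stay at 7% and 14%. The comparator is the natural indirect effect (NIE) in log-odds: logit P[Y(1, M(1))] - logit P[Y(1, M(0))]. Differences were taken before rounding.

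| a | b | c' | c - c' | share of c | NIE | share of c |
|---|---|---|---|---|---|---|
| 0 | 0.5 | 0.790 | -0.018 | -2% | 0 | 0% |
| 0 | 1.0 | 0.850 | -0.078 | -10% | 0 | 0% |
| 0 | 1.5 | 0.951 | -0.179 | -23% | 0 | 0% |
| 0.2 | 0.5 | 0.690 | 0.082 | 11% | 0.097 | 13% |
| 0.2 | 1.0 | 0.650 | 0.122 | 16% | 0.179 | 23% |
| 0.2 | 1.5 | 0.651 | 0.121 | 16% | 0.238 | 31% |

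At 9% versus 16%, the three zero-mediation rows become -3%, -12% and -26%, and the last row becomes 20% against 36%. On the risk scale, the indirect effect in the last row of the table is 0.0262 of 0.07, or 2.6 of the 7 points.

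**Step 2, order.** Suppose that quitting raises PCS by d points, PCS has no effect on quitting, and the arm affects PCS only through quitting: M = dY + e. Take d = 2 and residual SD 1.7 (both assumed; the plan quotes a PCS SD of 1.96, so 2 points is about one SD). True mediation through PCS is zero.

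- Arm difference in PCS: 2 × 0.07 = 0.14.
- Mean within-arm variance of Y: (0.07 × 0.93 + 0.14 × 0.86)/2 = 0.0928.
- Linear-probability slope of Y on PCS given arm: 2 × 0.0928 / (4 × 0.0928 + 1.7²) = 0.1855/3.261 = 0.0569. Spurious share by c minus c': 0.14 × 0.0569 / 0.07 = 11%.
- Logistic slope: 2/1.7² = 0.692. Spurious share by product of coefficients: 0.14 × 0.692 / 0.771 = 12.6%, about 13%.
- Logistic c minus c' in the same setting: about 0.

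The size depends on d. With d = 1 both spurious shares are about 3%. With d = 3 they are 22% and 28%.

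**Step 3, order, when the arm also raises the mediator directly.** Let M = aX + dY + e with SD 1 and no path from M to Y. Fits to 2,000,000 simulated participants with a = 0.2 gave a logistic c minus c' of 0.201 out of c = 0.782 (26%) at d = 1, and 0.300 out of 0.782 (38%) at d = 1.5. So the logistic difference is not generally protected.

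**The case against.** Several stronger readings are tempting, and the documents do not support them.

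- *The plan subtracts logistic coefficients.* The mediation section does not say so. This is inferred from the logistic model for the primary outcome and from the logistic model for NRT. A linear-probability version would have no non-collapsibility, and an unseen analysis plan may name the link. But the article does fix c minus c' as the mediated component, and the linear version still meets the order problem in Step 2.
- *c minus c' is never a mediated effect.* That is too strong. For a weak mediator (b = 0.5, a = 0.2) it gives 11% against 13%. The large distortions need a strong mediator: b = 1.5 is an odds ratio of about 4.5 per SD.
- *All mediators are measured at the outcome visit.* They are not. Quitline contact is dated from records and can precede the outcome window. Behavioural strategies have no stated timing. NRT is reported at 6 months, but the recall window is not shown, so the report may cover earlier use.
- *Reverse causation by itself corrupts logistic c minus c'.* In Step 2 it does not. The 11% and 13% belong to the linear-probability difference and the product of coefficients.
- *PCS certainly has a single follow-up value.* Internal Processes says so, but Hypotheses 1a and 2a speak of averaged and repeated follow-up PCS. The article contradicts itself here.
- *Engagement is a declared mediator.* It is not in the list of mediators, and the path figure is not shown. It appears only in the narrative chain.

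It is also fair that this analysis is secondary and described as exploring pathways.

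**Conclusion.** The concern holds in a limited form. The article defines the mediated component of a binary outcome as c minus c' without naming a scale. On the logistic scale, which is the likely one, this is biased towards too little mediation: at 7% versus 14%, by -2% to -23% of c when nothing is mediated, and 16% instead of 31% in the strongest case tabulated with real mediation. These sizes rest on assumed mediator strengths and are small for weak mediators.

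The order problem applies clearly to PCS if Internal Processes is correct, possibly to NRT, and not to quitline use. Its size, about 11% to 13% spurious mediation, rests on the assumed 2-point rise and residual SD of 1.7. The planned SEM does not settle order: the reasons given for it are multistep paths and measurement error, and fit indices do not show which variable came first. The primary analysis is untouched.

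**What to change.** 1. Replace c minus c' with natural direct and indirect effects on the risk-difference scale, with bootstrap intervals, adjusting for baseline PCS and other baseline confounders of mediator and outcome.
2. Base mediation claims on mediators dated before the 7-day outcome window, such as the first completed quitline call.
3. Reconcile the PCS schedule in Internal Processes with the averaged and repeated PCS in Hypotheses 1a and 2a. If PCS after randomisation exists only at 6 months, report it as an association with cessation and not as a mediator. Apply the same caution to NRT unless its recall window places use before the outcome window.
4. Keep engagement in Aim 1. Comparison participants receive no rated messages, so the variable is undefined for them and should not be entered as a mediator in a two-arm SEM.

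The cost is revised analysis wording and standard mediation software, with no new data. The downside is a weaker mechanism claim for PCS.

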**Figure 1 figure1:**
[figure not shown]
Hypothesized path model depicting associations among constructs. NRT: nicotine replacement therapy.

#### Qualitative Interview Analysis

We will transcribe the interviews verbatim and will use the rapid qualitative analysis method to code the transcripts. The rapid qualitative method uses triangulation and iterative data analysis to quickly develop a preliminary understanding of a situation from the insider’s perspective [45-47]. In this method, primary topics or “domains” will be taken from the topics addressed in the interview guide to create summary templates. Two research team members will each code at least 10% of the interview transcripts, and coding checks will be completed to ensure interrater reliability. We will use the summary templates to create a matrix to analyze each domain’s depth and breadth of data. From these, we will identify study themes and subthemes using the matrix. The research team will collaboratively and iteratively review, discuss, and sort the data to refine the initial themes and subthemes and highlight the most salient quotes. Recordings collected during interviews will be deidentified using subject ID numbers. No identifiable information, such as a full name, will be collected in the recording. Identifiers will be collected separately and will be stored in an encrypted form. Recordings will be transcribed and deidentified. They will be stored in a secured UMass Chan drive specified for the study within the UMass Chan IS regulated environment, where only UMass Chan study staff will have access to them. Recordings, and all other data collected in this study, will be retained and destroyed in accordance with Standard Operating Procedure Human Research Protection-800. Transcripts of audio or video recordings as well as the audio or video recordings themselves will be fully destroyed 6 years from the conclusion of the study period or at the request of the individual to whom that data belongs.

